### Ancillary and post-trial care

The subjects enjoy insurance protection while participating in the research project. The Ulm University Hospital and its employees involved in the study (study doctors, other staff) are covered by liability insurance if the test subjects are harmed through their fault. The subjects are also insured for accidental travel to and from the study centre.

### Amendments

In the event of protocol amendments, the date of each amendment will be accompanied by a description of the change and the rationale.

### Sponsor

Ulm University Medical Centre, [name] is the trial sponsor. The sponsor is not involved in the design of the study, manuscript writing or collection of data, and the sponsor will not be involved in data analysis or interpretation and manuscript writing in the future.

### Dissemination

The results of this protocol study will be published in peer-reviewed journals as well as at national and international conferences. A publication and authorship agreement between all project partners was agreed, which regulates the procedure for publications in detail.

### Access to data

Principal Investigators will be given access to the cleaned data sets under conditions defined in the publication agreement. Analysis data sets do not contain identifying participant information.

## Discussion

This study is the first to assess the effects of a structured implementation of a patient version of a psychiatric treatment guideline. The results will shed light on the effects of a structured implementation of such patient guidelines and will provide insights how patients guidelines can be implemented.

Some limitations of the study should be noted. For example, recruitment will take place in clinics; thus, only patients with inpatient stays will be recorded. Furthermore, the assessment is limited to south-east Germany (Bavaria), so transferability of the results to other regions needs to be considered. In addition, the study will not cover the full range of patients with severe mental disorders, such as severe personality disorders (F60 - F61), severe anxiety disorders (F41) or severe obsessive-compulsive disorder (F42).

In addition, an imbalance may occur in the recruitment numbers between the two randomised groups, as the recruitment of subjects in one of the two groups could be more difficult than in the other (e.g., if the subjects do not want to participate without intervention). Therefore, the extension of the recruitment period may be necessary for one group to reach comparable sample sizes.

In the intervention group, difficulties may occur in maintaining the participation for both group sessions.

Furthermore, recruiting relatives may be difficult because relatives are often not easily accessible.

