### Recruitment procedure

The recruitment and data collection will be conducted from October 2019 to March 2021. Eligible patients will be approached and informed about the IMPPETUS study by the study staff to determine whether they would be willing to participate in the study, especially giving the consent to be willing to participate at a time point 6 months after intervention (t_2_). If the patients give their consent, a screening with the ‘Global Assessment of Functioning’ (GAF) and the ‘Health of the Nation Outcome Scales’ (HoNOS) will be carried out to identify patients with severe mental illness according to the definition above. The screening will be conducted as soon as possible after admission. For more details *see* Fig. 1.

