### Sample size

Sample size calculation was based on a two-step procedure due to the hierarchical data structure. In the first step, the sample size for an individual randomized study is calculated. Based on studies using the ‘empowerment in the process of psychiatric treatment of patients with affective and schizophrenia disorders (EPAS)’ scale [26], a medium effect (0.4 SD units) of the implementation intervention on the primary endpoint is expected. This effect is detectable with an error probability of 5% (alpha) and a power of 80% by a t-test for independent samples with a sample size of 2 × 100 participants (200 in total).

The second step takes the cluster structure of the data into account. We assume that each centre recruits 35 patients (m) on average. The design effect (DE) is needed for the inflation of the group sample size: DE = 1 + (m - 1) * ICC with the fixed cluster size m and the intra-cluster correlation coefficient ICC. We assume a liberal intra-class correlation coefficient of 0.02 to control for the correlation of the outcome of participants of the same centre. Thereby, the DE is 1 + (35–1) * 0.02 = 1.68, which gives a sample size of 200 × 1.68 = 336 patients. As every centre recruits 35 patients on average, 10 centres are needed for the trial. Due to the severity of the disease in the patient population, case number planning assumes that 70% of patients can be reached 6 months after t_0_, so that an oversampling to (35/0.7) 50 patients per study centre will be recruited, resulting in 10 centres * 50 patients = 500 participants (2 × 250) as the overall sample size. This 70% estimate is based on experiences at the Günzburg site from three studies conducted with similar populations [27–29].

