## Trial status

Protocol Version: 1.3, Date: 14. October 2019;

Date of first enrolment: 28. October 2019;

Estimated date of the end of recruitment: 31. March 2021.

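### Recruitment may be extended in one arm only while the primary model has no enrolment-time term, and the stated end of data collection does not fit the six-month follow-up

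*Protocol article*

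**What the plan says.** **Extension.** Among its limitations, the protocol article (Discussion) notes that one arm may be harder to recruit than the other, for example "if the subjects do not want to participate without intervention". It concludes that "the extension of the recruitment period may be necessary for one group to reach comparable sample sizes". It gives no trigger, no limit and no analysis to go with such an extension.

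**Allocation and recruitment.** Whole centres are randomised (Randomisation) and the trial is non-blinded (Study design and setting). Study staff are trained before the start in the condition assigned to them (Interventions), and study staff approach and screen the patients (Recruitment procedure).

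**Primary model.** Under Statistical methods, EPAS at t2 is modelled on intervention, EPAS at t0, centre and centre size. Baseline variables enter if the full and the modified intention-to-treat populations differ on them. Other possible confounders are examined in analyses labelled exploratory. Only patients with a t2 value are analysed.

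**Dates.** Recruitment procedure: "The recruitment and data collection will be conducted from October 2019 to March 2021". Trial status: first enrolment on 28 October 2019, and "Estimated date of the end of recruitment: 31. March 2021". Data collection and management sets t2 at six months after t0 in both groups.

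**The concern.** If one arm stays open after the other has closed, its last patients are compared with nobody recruited at the same time. Any drift in EPAS outcomes over calendar time then falls on one arm. Drift is conceivable: the guideline was updated in 2019 (Background), its main contents are being put online, and control patients receive a flyer pointing to further sources (Interventions).

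The extension also treats the symptom. If numbers are unequal because patients who know their centre's allocation decide differently about taking part, recruiting for longer evens out the counts but leaves the two groups differently selected. The confirmatory model could correct for this only through EPAS at t0. The rule that adds covariates when the two analysis populations differ addresses loss to follow-up, not differential consent.

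The dates raise a separate issue. If recruitment and data collection both end in March 2021, patients enrolled in the last six months cannot have the primary outcome inside the stated window. An extension would widen that gap.

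**Working it through.** **1. The plan's own sample size.** Inputs from Sample size: "a medium effect (0.4 SD units) of the implementation intervention on the primary endpoint is expected"; "with an error probability of 5% (alpha) and a power of 80% by a t-test for independent samples"; "We assume that each centre recruits 35 patients (m) on average"; ICC 0.02; 70% reached at six months. Sidedness is not stated; two-sided is assumed.

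- The exact t-test gives 99.08 per arm, so 100 per arm, matching the stated "sample size of 2 × 100 participants (200 in total").
- Design effect = 1 + 34 × 0.02 = 1.68, and 200 × 1.68 = 336.
- 336 / 35 = 9.6, so 10 centres. 35 / 0.7 = 50 per centre, so 500 recruited.

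The stated figures reproduce.

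**2. What the extension buys.** With 5 centres per arm and m evaluable patients per centre, in SD units:

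- variance of an arm mean = (1 + (m − 1) × 0.02) / (5m)
- SE = square root of the sum over both arms
- power = Φ(0.4 / SE − 1.96)

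As planned (35 and 35): 2 × 1.68 / 175 = 0.0192, SE 0.1386, power 82.3%.

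One arm short and not extended, the other at 35:

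| Shortfall | m in short arm | Variance | SE | Power | Loss (points) |
|---|---|---|---|---|---|
| 10% | 31.5 | 0.0198 | 0.1408 | 81.1% | 1.2 |
| 20% | 28 | 0.0206 | 0.1435 | 79.6% | 2.7 |
| 30% | 24.5 | 0.0216 | 0.1470 | 77.7% | 4.6 |
| 50% | 17.5 | 0.0248 | 0.1575 | 71.9% | 10.4 |

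At a fixed total, imbalance itself matters little: 40 and 30 per centre raises the variance by 1.2%, and 45 and 25 by 5.2%. An extension adds patients, however, so the table is the relevant comparison. These figures use the normal approximation. A t-test on 8 degrees of freedom starts lower (71.6% as planned) and shows a similar pattern (68.6% at a 20% shortfall, 60.6% at 50%).

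**3. What the extension risks.** Recruitment lasts T = 17.1 months (28 October 2019 to 31 March 2021). If the slower arm recruits uniformly at a fraction r of plan:

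- extra months to reach 50 per centre = T / r − T
- share of that arm with no concurrent comparator = 1 − r
- difference in mean enrolment date = half the extra months
- bias = yearly trend × difference in months / 12

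The trend of 0.1 to 0.2 SD per year is an assumption; the protocol gives none.

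| r | Extra months | Non-concurrent share | Difference in mean date (months) | Bias (SD) |
|---|---|---|---|---|
| 0.8 | 4.3 | 20% | 2.1 | 0.02 to 0.04 |
| 0.7 | 7.3 | 30% | 3.7 | 0.03 to 0.06 |
| 0.5 | 17.1 | 50% | 8.6 | 0.07 to 0.14 |

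**4. The dates.** From 28 October 2019 to 31 March 2021 is 521 days. Patients enrolled after 30 September 2020, in the last 182 days, reach t2 after March 2021: 182 / 521 = 35%. Under uniform accrual that is about 175 of 500. If March 2021 were a hard stop, about 325 × 0.7 = 228 patients would be evaluable (22.8 per centre), against 500 × 0.7 = 350. Power by the formula above would be about 71% instead of 82%.

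**The case against.** The strongest reply is that the extension is conditional. It stands among the limitations and is worded as something that may become necessary. A reader might infer that the trial plans to recruit the arms over different periods, or that the primary comparison is biased. The document supports neither. The common recruitment period stays concurrent, only the tail is exposed, and bias requires a trend for which the protocol gives no evidence. This stands, and it limits the weight of the point.

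A reader might also infer from the 1.2% and 5.2% figures that the extension buys almost no precision. That holds for shortfalls up to about 20%, but not at 30 to 50%, where it protects roughly 5 to 10 power points. The protocol gives no expected shortfall.

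Covariate choice is often left to an analysis plan, which is not at hand. But the article itself fixes the confirmatory model and assigns other confounders to exploratory analysis, so this is a stated choice rather than an omission.

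On the dates, a reader might infer that t2 will be missing by design for late recruits. That follows only if one sentence in Recruitment procedure is taken as a hard stop on follow-up. Trial status dates recruitment only, calls the date estimated, and is compatible with follow-up to about September 2021. What remains is a contradiction to reconcile, not evidence of lost outcomes.

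**Conclusion.** The concern holds as a weakness in a contingency, together with a separate inconsistency in dates. If the one-arm extension is used, the protocol contains no protection against calendar-time differences and no confirmatory adjustment for differential consent beyond EPAS at t0. For 20 to 30% shortfalls the possible bias is modest, 0.02 to 0.06 SD against a target of 0.4 SD. This rests on uniform accrual within each arm and the assumed trend. The power at stake at those shortfalls is also modest, about 3 to 5 points at ICC 0.02. With a 50% shortfall both grow: 0.07 to 0.14 SD and about 10 points. The trade-off is therefore not one-sided, but common recruitment dates avoid it.

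The three statements on dates cannot all hold for patients enrolled after September 2020, about 35% of the window under uniform accrual. The figure of 228 evaluable patients is conditional on the literal March 2021 stop and 70% retention.

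**What to change.** 1. Use one recruitment closing date for all centres in both arms. If one arm is slow, extend both or accept unequal numbers.
2. If one arm is extended all the same, include enrolment period in the primary model and report an analysis limited to the period when both arms were recruiting.
3. Pre-specify in the confirmatory model a short set of baseline covariates already collected: diagnosis group (F2x or F3x), GAF, HoNOS, age and sex.
4. State that data collection runs until the last t2, about the end of September 2021 if recruitment ends on 31 March 2021. Align the text at the same time: Recruitment procedure places t2 six months after the intervention, Data collection and management six months after t0.

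**Cost.** Items 2 to 4 need wording and no new data. Item 1 costs either power (the first table) or surplus recruits. The faster arm enrols 50 / 17.1 = 2.9 patients per centre per month, so 4.3 or 7.3 extra months add about 12.5 or 21.4 per centre. Over 5 centres that is roughly 63 or 107 patients, each with three interviews.

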## Trial status

Protocol Version: 1.3, Date: 14. October 2019;

Date of first enrolment: 28. October 2019;

Estimated date of the end of recruitment: 31. March 2021.

## Data Availability

The datasets used and analysed during the current study will be available from the corresponding author on reasonable request. Informed consent materials are only available in German. They are available on request from the corresponding author.

## Abbreviations

BAS: Burden Assessment scale
CAN-EU: Camberwell Assessment of Need
CSSRI: Client Sociodemographic and Service Receipt Inventory
DE: Design effect
DGPPN: German Association for Psychiatry, Psychotherapy and Psychosomatics
EPAS: Empowerment in the Process of Psychiatric Treatment of Patients with Affective and Schizophrenia Disorders Scale
EQ-5D-5 L: EuroQol
FCS: Fully conditional specification
F-INK: Questionnaire to Assess the Participation and Social Inclusion of the Patients
GAF: Global Assessment of Functioning
HEA: Health Economic Evaluation
HoNOS: Health of the Nation Outcome Scales
ICC: Intra-cluster correlation coefficient
ICUR: Incremental cost-utility ratios
IMPPETUS: Implementation of the Patient Version of the Evidence-based Guideline for Psychosocial Interventions for Patients with Severe Mental Illness
modITT: Modified intention-to-treat
MWTP: Maximum willingness to pay
QALY: Quality-adjusted life year
S3 guideline: Evidence and consensus-based guideline
SD: Standard deviation
t_0_: Assessment shortly after admission (baseline)
t_1_: Assessment 2 weeks after visiting both parts of the group sessions (intervention group) or 6 weeks after t_0_ (control group)
t_2_: Assessment 6 months after t_0_
TAU: Treatment as usual
WHOQOL-BREF: World Health Organization’s Quality of Life Instrument-abbreviated version
ZUF-8: German satisfaction questionnaire
